### Additional consent provisions for collection and use of participant data and biological specimens {26b}

If a patient withdraws consent, their data will be removed from the database and will not be used for analysis. In the case of study discontinuation, data may be retained if authorized by the patient. In such cases, primary and secondary outcomes will be assessed at the date of discontinuation.

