### Criteria for discontinuing or modifying allocated interventions {11b}

Neither the measurements nor the game manipulation produces any significant harmful side effects, as the game does not have graphic depictions of violence, and any of our measurements are not invasive. Therefore, we do not anticipate the need to modify the intervention during the study.

Patients can withdraw from the study at any time without adverse consequences for the patient. The investigator can also terminate a patient's participation in this study if the patient is uncooperative and/or does not attend the study visits. Patient data collected to date will be included in the analysis. If too much data is lost, the patient will be replaced by a new patient. The study will be terminated early in the event of serious adverse events, such as aspiration or vomiting.

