Secondary outcomes in this study were quality of life, nutritional status, satisfaction and adherence. The swallowing quality of life (SWAL-QOL) questionnaire consists of 10 subscales and a symptom scale (14 items) to assess the severity of dysphagia symptoms. Scores range from 0 to 100, with lower scores indicating greater impairment of quality of life from dysphagia [24]. Body mass index (BMI) and Mini Nutritional Assessment Short Form (MNA-SF) were used to assess the nutritional status of the dysphagia patients. BMI is one of the most commonly used nutritional assessments among adults [25]. MNA-SF is commonly used to screen patients for malnutrition or risk of malnutrition with high sensitivity and specificity [26]. MNA-SF in combination with BMI showed higher accuracy [27]. The satisfaction questionnaire was designed based on the literatures. There are 15 items, involving 3 dimensions: training mode content setting, training mode format setting, and self-subjective feeling, and scored on a 5-point Likert scale. The higher the score, the more satisfied the patients were with the video-game training. Adherence was considered good if the patient could complete more than 80% of the training sessions of the corresponding training program; average if the patient could complete 50% to 80% of the training sessions; and poor if the patient could complete less than 50% of the training sessions. Patients are considered to have completed their training when they have completed more than 12 training sessions [28].

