## Assignment of interventions: allocation

### Sequence generation {16a}

To avoid selection bias, an independent statistician will use R software to generate a set of random numbers. The list of random numbers will consist of a set of numbers ranging from the number 1 to the number 78, and they will be randomly divided into intervention group and control group. During the randomization process, the R function "sample ()" will be used to ensure the same group size. The intervention group will be named "Group 1" and the control group will be named "Group 2".

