## Statistical methods

### Statistical methods for primary and secondary outcomes {20a}

An intention-to-treat analysis will be performed, and the last available measurement will be used when data were lost due to dropout. Statistical analysis will be performed using SPSS 29.0. Statistical significance of all outcome variables will be established at *P* < 0.05.

All continuous data will be tested for normality, and nonparametric tests will be used for non-normally distributed data. Data conforming to normal distribution will be expressed as mean ± standard deviation (SD), and data with non-normal distribution will be expressed as median (interquartile range).

Comparisons of continuous data of two groups at the same time will be analyzed using independent samples t tests or rank sum tests, and comparisons of two groups of rates will be performed using chi-square test or Fisher exact test [31].

Comparison of continuous data trends over time between different groups at different times, if data normality is present, we will perform a series of repeated measures analysis of variance (ANOVA) for each outcome measure to assess differences between time (4 weeks and 1 month post) and between study groups, as well as interactions between time and study groups. For these analyses, the assumptions of sphericity and homogeneity of variances are tested using Mauchly and Levene tests [32]. If the assumption of sphericity is violated, the Huynh–Feldt correction is applied [32].

If the normality assumption is not met, the linear mixed model will be used for analysis, the comparative analysis at each time was performed using the nonparametric statistical Mann–Whitney U test and its own control two-way comparison using the nonparametric statistical Kruskal–Wallis rank sum test [33].

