### Methods in analysis to handle protocol non-adherence and any statistical methods to handle missing data {20c}

An intention-to-treat analysis will be performed, and the last available measurement will be used when data were lost due to dropout. To address missing data, the multiple imputation method will be employed. For participants randomized to the intervention group who do not adhere to the intervention, a per-protocol analysis will also be performed to assess the impact of non-adherence on the study outcomes.

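### An undefined rule for replacing randomised patients leaves the intention-to-treat population open, and the supplementary per-protocol analysis covers one arm only

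*Protocol article*

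**What the plan says.** **Analysis population.** Statistical methods {20a} states: "An intention-to-treat analysis will be performed, and the last available measurement will be used when data were lost due to dropout". Section {20c} repeats this.

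**Replacement.** Criteria for discontinuing or modifying allocated interventions {11b} lets patients withdraw, and lets the investigator end participation for lack of cooperation or missed visits. It continues: "Patient data collected to date will be included in the analysis". The next sentence is: "If too much data is lost, the patient will be replaced by a new patient".

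**Allocation and size.** Sequence generation {16a} describes "a set of numbers ranging from the number 1 to the number 78", split into equal groups. Sample size {14} gives 31 per group, raised by 20% for dropout to a total of 78.

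**Data retention.** Additional consent provisions {26b} says: "If a patient withdraws consent, their data will be removed from the database and will not be used for analysis". For the other case it says: "In the case of study discontinuation, data may be retained if authorized by the patient". Retention {18b} makes collection of outcomes up to withdrawal subject to the participant's consent.

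**Per-protocol analysis.** Section {20c} adds such an analysis with this scope: "For participants randomized to the intervention group who do not adhere to the intervention".

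**The concern.** Intention-to-treat means that everyone randomised is compared in the arm to which they were randomised. A rule that swaps a randomised patient for a new one, triggered by an unspecified amount of missing data, acts after randomisation and is discretionary as written. If the replaced patient leaves the analysis, the groups compared are no longer the groups randomised. Missing data need not be balanced. The protocol expects high compliance with the game {11c} and describes conventional training as tedious and poorly adhered to (Background), so the patients eligible for replacement could differ between arms. This is plausible but not shown.

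The data-retention rules raise a related problem. For a patient who discontinues, one section keeps the data outright and another keeps them only with authorisation. Two people following the protocol could build different datasets.

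The per-protocol analysis is a separate matter. If it removes poor adherers from the game arm and keeps them in the control arm, the two sides are selected differently and the result would favour the game if poor adherers swallow less well.

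**Working it through.** **1. Reproduce the plan's numbers (Sample size {14}).**
Inputs: FOIS means 5.40 and 4.40, SDs 1.70 and 0.80, alpha 0.05, power 90%.
- Pooled SD = sqrt((1.70² + 0.80²)/2) = 1.329; d = 1.00/1.329 = 0.753.
- Two-sample t test, one-sided alpha 0.05: 31 per group (power 0.901). This matches the stated 31.
- Dropout: 31/(1 − 0.20) = 38.75, rounded up to 39 per group, 78 in total. This matches the stated 78.

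The 31 reproduces only with a one-sided test; a two-sided test needs 39 per group. That is a different point and is not pursued here.

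**2. Is replacement needed?**
- Allowance already built in: 39 − 31 = 8 per group.
- After 20% loss: 78 × 0.80 = 62.4, so about 62 patients with data, which is the plan's own target.

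Replacement would pay a second time for dropout that the 78 already covers.

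**3. What could replacement do to the comparison?**
Let r be the number replaced. Then 78 + r patients are randomised. If the replaced patients are left out, the share missing from the comparison is r/(78 + r). The protocol gives no value for r, so these are assumed:
- r = 4: 4/82 = 4.9%
- r = 8: 8/86 = 9.3%
- r = 16: 16/94 = 17.0%

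If replaced patients stay in, the share is zero and the newcomers are simply extra patients. The text does not say which applies. In both cases the newcomers fall outside the 78-number list, and the article does not say how they are allocated. Giving a newcomer the lost patient's arm would make that allocation known in advance.

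**4. Data-retention rules side by side.**
- Withdrawal of consent: removed and not analysed {26b}.
- Discontinuation: retained if the patient authorises it {26b}.
- Withdrawal from the study or termination by the investigator: included, with no condition {11b}.
- Withdrawal: outcomes up to that time collected with consent {18b}.

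The first rule concerns its own event. The second and third cover overlapping events and disagree on whether authorisation is needed.

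**5. One-armed per-protocol exclusion.**
Let p be the share of non-adherers in the game arm and g the FOIS gap between adherers and non-adherers. The mean of the whole arm is (adherers' mean) − p × g, so dropping non-adherers raises the arm mean by p × g. With no exclusions among controls, the between-group difference moves by the same amount. Assumed ranges (neither is in the protocol): p from 0.10 to 0.30, g from 0.5 to 1.0.
- Lowest: 0.10 × 0.5 = 0.05 FOIS points
- Highest: 0.30 × 1.0 = 0.30 FOIS points

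Against the planned difference of 5.40 − 4.40 = 1.00, this is 5% to 30%, arising with no true effect. If the game arm adheres as well as the protocol expects, p lies towards the low end.

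**The case against.** The best defence is the sentence just before the replacement rule, which keeps data collected to date in the analysis. Read with the missing-data methods in {20a} and {20c}, it allows a replaced patient to remain in the analysis with the new patient as an addition. That reading is open. A reader might infer that intention-to-treat is lost outright; the documents do not support that. They support the narrower statement that the analysis population is not fixed.

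Other stronger readings also fail:
- **The per-protocol analysis undoes intention-to-treat.** It is performed in addition, so it cannot.
- **Unblinded staff decide on replacement.** Participants and therapists are unblinded {17a}, but no section says who decides.
- **A replacement has no random allocation.** The article is silent, and a full protocol may cover it. What stands is that the stated list ends at 78.
- **Deleting data on withdrawal of consent is a bad analysis choice.** It is a separate event from discontinuation and may be an ethics condition. It needs to be declared as an exception.
- **The adherence cut-offs contradict each other.** Outcomes {12} grades adherence, with good meaning more than 80% of sessions, and separately states: "Patients are considered to have completed their training when they have completed more than 12 training sessions". These are two constructs. Which one defines the per-protocol set may be left to the analysis plan.
- **Assessment at the discontinuation date replaces weeks 4 and 8.** Section {26b} does not say that the scheduled visits are dropped.

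The objection that the 0.05 to 0.30 figure is assumed and concerns only a secondary analysis is correct.

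**Conclusion.** The point holds in three limited parts.

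1. **Replacement rule.** It has no threshold, leaves the status of replaced patients unstated, and sits badly with the promised intention-to-treat analysis. It is not needed to reach the plan's own target of 31 per group. Its effect ranges from none, if replaced patients stay in, to 4.9%–17.0% of randomised patients missing for an assumed 4 to 16 replacements. The direction and size of any bias in the primary result cannot be derived from the documents.
2. **Data after discontinuation.** Sections {11b} and {26b} conflict on authorisation and must be reconciled.
3. **Per-protocol analysis.** As worded it is asymmetric. If non-adherers do worse, it favours the game by share × gap, 0.05 to 0.30 FOIS points under the assumed inputs. This concerns the supplementary result only.

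The first part matters most because it affects the primary comparison, and a patient replaced during conduct may not be recoverable for analysis afterwards.

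**What to change.** - Delete the replacement sentence in {11b} and state that all 78 patients are analysed in the arm to which they were randomised.
- Reconcile {26b}, {11b} and {18b}: data collected before discontinuation are kept, with permission sought at consent. If data are deleted on explicit withdrawal of consent, state this as an exception to intention-to-treat and report the number by arm.
- Seek the week 4 and week 8 assessments from patients who stop training but have not withdrawn consent.
- In {20c}, define the per-protocol set by the same session cut-off in both arms and label the analysis supportive.

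The cost is wording in the protocol and consent form. The sample size of 78 does not change on account of this point. The downside is slightly fewer complete cases than replacement would give. The protocol describes the trial as not yet recruiting, so on its stated timeline the changes could be made before any patient is affected.

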## Abstract

**Background:**

Dysphagia can lead to serious complications such as aspiration and aspiration pneumonia, timely and effective rehabilitation training can improve the swallowing function of patients. However, the conventional rehabilitation training methods used in clinical settings have shortcomings such as poor adherence of patients. We present the study design of a randomized controlled trial that evaluated whether video-game based swallowing rehabilitation training can effectively improve swallowing in patients with dysphagia and whether it has additional benefits compared with conventional training methods to improve swallowing function and training compliance among patients with dysphagia.

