## Introduction

### Background and rationale {6a}

Dysphagia is a clinical phenomenon in which the jaw, lips, tongue, soft palate, pharynx, esophagus, and other organs are structurally and/or functionally impaired, preventing the safe and effective delivery of food from the mouth into the stomach [1]. Decreased muscle mass, reduced salivary secretion, and neurological disorders can lead to patients suffering from dysphagia [2]. A global survey reported that 26.2% of older adults, 8.1%-80% of stroke patients, and 11%-81% of Parkinson's patients had dysphagia [3]. Patients have increased complications such as aspiration, aspiration pneumonia, malnutrition, and psychological and social interaction disorders due to dysphagia, which leads to reduced immune response, prolonged patient length of stay in hospitals, increased patient mortality, and hospitalization costs [4].

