### Composition of the data monitoring committee, its role and reporting structure {21a}

Data monitoring committee (DMC) was not specified for this study. This decision was made on the basis that no serious adverse events would occur in this study.

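### As worded, the discontinuation criteria {11b} would end the whole trial on serious events such as aspiration, a known complication of the enrolled condition; a participant-level stop may be meant but is not stated

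*Protocol article*

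**What the plan says.** All places are in the protocol article.

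- **Criteria for discontinuing or modifying allocated interventions {11b}**: "The study will be terminated early in the event of serious adverse events, such as aspiration or vomiting". The sentence is mandatory and does not mention relatedness to training or study arm. Three sentences earlier, the same paragraph lets the investigator end one patient's "participation in this study if the patient is uncooperative" or misses visits.
- **Abstract, Background**: "Dysphagia can lead to serious complications such as aspiration and aspiration pneumonia".
- **Background and rationale {6a}**: "Patients have increased complications such as aspiration, aspiration pneumonia, malnutrition", among others, attributed to dysphagia.
- **Eligibility criteria {10}**: the first inclusion criterion is a diagnosis of dysphagia, so every participant has the condition.
- **Additional consent provisions {26b}**: "In the case of study discontinuation, data may be retained if authorized by the patient"; in those cases "primary and secondary outcomes will be assessed at the date of discontinuation".
- **Plans to promote participant retention {18b}**: for participants who withdraw, outcome data are sought only as far as the withdrawal date, with consent.
- **Statistical methods {20a}**: "An intention-to-treat analysis will be performed, and the last available measurement will be used" where dropout leaves data missing.
- **Adverse event reporting and harms {22}**: serious adverse events go to an ethics committee and are discussed with the participant's doctor. Closing the trial is not mentioned.

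**The concern.** A rule that closes a trial should respond to evidence that the intervention does harm. This one, as worded, responds to an event that the article says the disease itself produces. A serious aspiration caused by the underlying dysphagia, even in a control patient who never used the game, would meet the trigger. The trial would then end before its primary comparison, for a reason that says nothing about the game.

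If only the affected participant's training is meant to stop, that danger disappears. The wording would still be wrong, because each time the trial continued after such an event, staff would be acting against the text.

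A second consequence arises under the participant-level reading. A participant who stops training after an event would, under {26b}, be assessed on the day of stopping. Under {20a} that value would then stand in for the 4- and 8-week results, although the participant might be willing to attend both visits.

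**Working it through.** The article gives no figure to reproduce. The check is a comparison of sections, followed by an illustration of what the literal rule would do.

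**Step 1. What does the sentence cover?**

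| Question | Evidence | Points to |
|---|---|---|
| Subject of the sentence | {11b} names the study, yet refers to a patient's participation when one patient is meant | whole trial |
| Heading of the section | {11b} concerns discontinuing allocated interventions | one participant |
| Neighbouring sentences | withdrawal, ending participation, data kept, replacement of a patient | one participant |
| Usage in {26b} | study discontinuation refers to one patient | one participant |
| Usage in {22} | the study is said to be halted when a participant has any discomfort, which can only mean a session | one participant |
| Explicit limit to one participant | none in any section | unresolved |

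The wording of the sentence favours the whole trial and its surroundings favour one participant. Nothing in the article decides between them.

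**Step 2. Is the trigger a background event?** For aspiration, yes: the Abstract and {6a} name it as a complication, and {10} requires dysphagia in everyone. The article does not say this of vomiting, and the point does not need it.

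**Step 3. Illustration under the literal reading.** Inputs: n = 78 (Abstract, Methods; Sample size {14}), allocated 1:1 (Trial design {8}), so 39 controls. The per-patient risk p of a serious triggering event over the trial is not in the article and is assumed to lie between 0.1% and 2%. Participants are treated as independent.

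- One event is enough: 1 − (1 − p)^78
- The plural in the sentence means two affected patients: 1 − (1 − p)^78 − 78p(1 − p)^77
- At least one event among controls: 1 − (1 − p)^39
- Expected number affected: 78p

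| Assumed p | One event ends the trial | Two patients needed | At least one event in controls | Expected affected |
|---|---|---|---|---|
| 0.1% | 7.5% | 0.3% | 3.8% | 0.08 |
| 0.5% | 32% | 6% | 18% | 0.39 |
| 1% | 54% | 18% | 32% | 0.78 |
| 2% | 79% | 46% | 55% | 1.56 |

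Worked line at p = 1%: 1 − 0.99^78 = 1 − 0.457 = 0.543. If one event is enough, closure becomes more likely than not once p exceeds 1 − 0.5^(1/78) = 0.0088, or about 0.9%.

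**Step 4. The participant-level reading.** The chance that an event of this kind closes the trial is then zero, and no figure in the table applies.

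**The case against.** The strongest reply is that a stop for one participant is obviously meant. The heading, the neighbouring sentences and the loose usage in {22} and {26b} all support that, and {22} handles serious events through the participant's doctor with no word of closing the trial. This makes the participant-level reading quite plausible. It does not make it the stated rule, since the same paragraph has separate wording for ending one patient's participation.

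The reply on size also stands. The probabilities rest wholly on assumed rates. The rule covers only serious events, {10} excludes patients with serious heart, lung, liver or kidney disease, and the exercises as described involve no food or liquid. A reader might infer that the trial is likely to be closed early. The article does not support that, because it gives no rate and at 0.1% the chance is 7.5% or less.

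Two stronger readings are tempting and should not be drawn:

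- *The data monitoring section {21a} contradicts {11b}.* It says "This decision was made on the basis that no serious adverse events would occur in this study". That is an overconfident expectation, not a conflict with a plan for what to do if such an event occurs. The auditing section {23} already gives the sounder reason, low intervention risk.
- *The serious-event path in {22} leaves out aspiration.* Its examples are fractures and bleeding, but they form an open list that already covers a serious aspiration.

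Finally, event thresholds and the detail of causality assessment are matters that a journal article commonly leaves to the full protocol. Their absence is not the point here. The point is a rule that the article does state, in words that reach too far.

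**Conclusion.** The point holds as a defect in one stated rule. Followed as written, {11b} requires the whole trial to end on serious events that include a complication of the enrolled disease, in either arm and whatever the cause. The article does not establish that this was intended, and a stop for one participant may be meant.

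The finding rests on the text and not on any event rate. The size under the literal reading is 7.5% to 79% for assumed risks of 0.1% to 2%, if one event is enough, and 0.3% to 46% if two affected patients are needed. Under the participant-level reading there is no trial-level risk. What then remains is the wording and the loss of later assessments in participants who stop training. The sample size and the choice of analysis are unaffected. The sentence should be changed, since the correction is cheap and settles how the trial is run after such an event.

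**What to change.** 1. **{11b}**: replace the sentence with a statement that a serious adverse event, for example aspiration or vomiting, stops that participant's training and not the trial. Reserve closure of the whole study for serious events judged related to the training, after the ethics committee report that {22} already requires. The article names the committee differently in {9}, {5d} and {22}, so say which one is meant.
2. **{26b} and {18b}**: state that participants who stop training but still consent are assessed at 4 and 8 weeks. Keep assessment at the date of discontinuation for those who decline further follow-up. This fits the intention-to-treat analysis in {20a}.

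Rewording {21a} and {22} is optional and not part of this finding. No monitoring committee, extra staff, patients or new visits are needed.

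The cost is the wording changes plus assessments at already scheduled visits for the few who stopped training because of such an event: about 0.08 to 1.56 expected among 78 at assumed risks of 0.1% to 2% (78 × p).
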